#### Data collection

All findings including clinical and laboratory data will be documented by the investigator or an authorized member of the study team in the patient’s medical record and in the electronic case report form (eCRF). The eCRF will be created by using the electronic data capture System MARVIN by XClinical, which is used and established within the GPOH and available in all participating centers. All data will be reported and collected pseudonymized.

#### Primary outcome phase I

The definition for the phase I primary outcome DLT of the combination treatment is described above. Planned times for all safety assessments are listed in the visit plan in Additional file 4. Safety assessments include AEs (on the basis of the 5-grade scale defined in the Common Terminology Criteria for Adverse Events (CTCAE) v5.0), physical examinations, vital signs, weight, performance status, assessment of signs and symptoms, laboratory tests, ECGs and pregnancy tests.

#### Primary outcome phase II

The phase II primary outcome best response will be assessed at each follow-up scan prospectively according to the visit plan in Additional file 4. Study endpoints of response or progression will be based on RANO criteria for all CNS tumors [43] and RECIST for all solid tumors. Further disease specific response criteria can be applied in individual cases to the investigator’s discretion. MRI is the preferred modality, but alternative/additional modalities can be used if this is required for certain entities according to institutional or standard of care guidelines. All radiologic imaging will be submitted for blinded independent central review in a pseudonymized fashion at the study’s reference radiology within 2 working days. Importantly, progressive disease will only be confirmed after central review. As a secondary endpoint and in accordance with Borcoman et al. [44], for patients who continued treatment beyond progression in case of clinical benefit, response as assessed by iRECIST [45] or iRANO [46] will be performed.

### Sample size

Phase I (dose finding) will recruit patients regardless of their biomarker status. Dose finding in the older age cohort will recruit 3–12 patients (if the younger age cohort is not allowed to open due to too much DLTs in the first 3 patients of the older age cohort, the total number of patients would be 3). If dose finding is initiated in the younger age cohort, it will also require 3–12 patients. This will result in 3–24 patients in total. Patients entering the trial on RP2D in the phase I can seamlessly enter phase II. Patients will be allocated to the four separate cohorts A – D. The sample size in cohorts A, B and C will be restricted by availability of the patients with the biomarkers during the 3-year study recruitment period. The upper limit of patients planned to be recruited to each of the cohorts A, B and C is 20–25. Since the actual patient number is not known exactly, expected type 1 error rate and power are reported averaged over the range of patient numbers to be expected in each cohort. Given the choice of the criteria c_Futility_ and c_Activity_ in the Bayesian adaptive design and assuming that patient numbers between 20 and 25 are equally likely, the expected type 1 error rate is 6.6% and the expected power is 76%. No second interim analysis is planned for cohorts A, B and C. In cohort D recruitment is expected to be faster and the sample size can be determined on the basis of power and 1-sided alpha-level, using the same criteria for futility and efficacy as in cohorts A, B and C. The smallest sample size such that alpha is ≤5% and power ≥ 80% is *n* = 29, for type 1 error is 5.0% and power is 80.3%. The upper limit of patients planned to be recruited to cohort D is therefore 29. A second interim analysis is planned after 20 patients for this cohort. Analytical calculations of the operating characteristics were derived [38] and power calculations were made with the R package BDP2 Version 0.1.3 (from CRAN (https://CRAN.R-project.org/package=BDP2)) which is the core of the web tool BDP2 workflow (http://biostatistics.dkfz.de/BDP2/).

### Statistical methods

#### Primary outcome phase I

A description of safety will be provided on the whole safety population and by dose level. Description of the frequency and percentage of each AE related to the treatment will be provided. RP2D will be defined as the dose level for which at most one out of 6 patients experienced DLT during the priming week and the first cycle, unless otherwise recommended by DMC in collaboration with the coordinating investigator. The steering committee will consider drug related AEs occurring after the first cycle of combination therapy in assessment of overall tolerability.

#### Primary outcome phase II

The activity analysis will be done on the activity population (all patients included in phase II, treated at the RP2D and having received at least one cycle of treatment) and primary analysis will be carried out on each biomarker cohort separately. The final evaluation of activity is based on the same rules for posterior probability as defined for interim analysis.

The estimate of the best response rates (as defined by RECIST or RANO and after central imaging review) will be given with 90% confidence interval in cohorts A, B and C and the estimate of the best response rates will be given with 95% confidence interval in cohort D.

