## Methods/design

### Study design

INFORM2 NivEnt is an exploratory non-randomized, open-label, multinational and multicenter seamless phase I/II trial of nivolumab and entinostat in children and adolescents with relapsed / refractory or progressive high-risk solid tumors and CNS tumors. A schematic overview of the trial is provided in Fig. 1. Since the age spectrum comprises a broad range of physical development of the study patients, phase I is divided in 2 age cohorts: 12–21 years and 6–11 years (in the absence of a pediatric liquid formulation for entinostat, no patients younger than 6 years can be enrolled). Although one could argue that for adolescents no dose escalation is necessary since there is no biological reason to expect another RP2D [34], it was decided to include a dose escalation for adolescents since the available adult data is still immature. The separate dose escalations for children 6–11-year-old and adolescents 12–21-year-old was included to fulfill regulatory requirements. The two age cohorts will run independently and follow a 3 + 3 design with two dose levels [35]. With only two dose levels, a model-based phase I design such as the Continual Reassessment Method was considered but would not offer any advantage to the traditional 3 + 3 design. RP2D is the dose at which up to 1 of 6 patients experiences dose limiting toxicity (DLT). Assuming more similarity with adult data, the trial will start with the older age cohort. The younger age cohort starts if either of the following events occur: 0 of 3 patients of the older age cohort experience a DLT in the DLT observation period OR a maximum of 1 of 6 patients of the older age cohort experience a DLT in the DLT observation period. Patients entering the trial on RP2D can seamlessly enter phase II. In order to maximize the chance of detecting early signs of activity of the combination treatment, phase II consists of a biomarker defined four group (A - D) phase II basket trial. If patients harbor more than one biomarker fitting group A, B or C, they will be allocated according the following priority: A: highest, B: intermediate and C: lowest priority. The aim is to identify the biomarker cohorts in which the combination treatment shows promising activity, i.e. a response rate exceeding the historical response rate of p_0_ = 12% which was observed in a comparable pediatric patient population treated in phase I/II trials [3]. A response rate of p_1_ = 30% would be considered as the target response rate to be detected with high probability.

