
**Fig. 1 Fig1:**
[figure not shown]
Schematic study overview. Figure shows the workflow of the INFORM Registry molecular pipeline followed by the respective phase I and phase II of the INFORM2 NivEnt trial. WES, whole exome sequencing; LC-WGS, low coverage whole genome sequencing; RNA-Seq, RNA sequencing. ^a^ Or equivalently valid molecular pipelines

A Bayesian adaptive design will be used with the objective of stopping cohorts early which are showing no evidence of activity (stopping for futility) [36–38]. Interim analyses will be based on the Bayesian posterior probability distribution of the best response rate, r. Futility will be declared if the posterior probability that r is ≥ p_1_ is smaller than c_Futility_. Activity will be declared if the posterior probability that r is ≥ p_0_ is larger or equal to c_Activity_. The Bayesian model will be based on the Beta-binomial conjugate family. For futility, the prior is chosen as an optimistic Beta(p_1_, 1-p_1_), and for activity the choice is accordingly a sceptical Beta(p_0_, 1-p_0_). Every cohort will be evaluated separately. An interim analysis is planned after 10 patients. If recruitment allows, further interim analyses are planned every 10 patients. Based on the evaluation of the operating characteristics of the trial design, c_Futility_ was selected as 0.01 and c_Activity_. as 0.90 [37]. The resulting decision rules for futility and efficacy in terms of number of observed responders among enrolled patients are shown in Fig. 2. The probability of stopping for futility at first interim when the treatment is not active is at least 27.8% whereas it is only 2.8% for an active treatment with true response rate of 30%.

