**Fig. 2 Fig2:**
[figure not shown]
Decision boundaries for futility and efficacy in terms of number of observed responders among enrolled patients. The same criteria apply for interim and final analyses

Three scenarios are possible following interim analysis:
In case the efficacy criterion is met, no early stopping is planned. However, early evidence of efficacy may set in motion the conception of a subsequent phase II/III trial.In case neither the efficacy nor the futility criterion is met, recruitment will continue.In case the futility criterion is met, recruitment of patients will be suspended and the DMC will be notified. The DMC will advise the coordinating investigator whether to terminate or to amend the trial.

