#### Secondary outcomes

(Confirmed immune-related) response will be evaluated separately for CR and PR, and SD and DCR will be evaluated in addition, also using iRECIST and iRANO. DOR will be evaluated for all patients who experienced (confirmed immune-related) response. Starting time point will be the time when best response was determined. The event-time endpoints PFS, OS and TTR will be estimated using the Kaplan-Meier method, considering all the patients who started the treatment, whatever their compliance to treatment, including if the treatment was stopped prematurely for a reason other than disease progression. 95%-confidence intervals will be provided for the Kaplan-Meier estimates.

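### The primary phase II response analysis leaves out patients who do not receive one cycle, which favours declaring activity and departs from the denominator behind the stated error rates

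*Protocol article*

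**What the plan says.** Under Statistical methods, Primary outcome phase II, the activity analysis is done on "all patients included in phase II, treated at the RP2D and having received at least one cycle of treatment". No exception is made for patients who stop early because of progression, death or toxicity. The same section says that the final evaluation uses the same posterior-probability rules as the interim.

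Other parts of the article use a wider set:

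- **Decision rules.** Study design and the Fig. 2 legend give the boundaries as "number of observed responders among enrolled patients", and the legend applies them at interim and final alike.
- **Operating characteristics.** Sample size gives type 1 error and power at the numbers to be recruited (20–25 in each of A, B and C; 29 in D), with no allowance for patients who are not analysed.
- **Time-to-event endpoints.** Under Secondary outcomes, PFS, OS and TTR are estimated "considering all the patients who started the treatment, whatever their compliance to treatment".

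On timing, Dosing and dose adjustments sets 4-week cycles after a one-week priming phase. Primary end point phase II counts the best response on combination therapy within 6 cycles, assessed every 2 cycles by central review. Assessments and collection of outcomes puts these assessments 8 weeks apart.

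**The concern.** Membership of the primary analysis set depends on something that happens after treatment starts. A patient who leaves before one cycle has had no scheduled response scan, and response must occur under study therapy, so such a patient can hardly be a responder. The rule therefore removes failures and almost nothing else.

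In cohorts of 20 to 29 patients, one or two removals can decide the result. An inactive combination becomes more likely to be declared active, and less likely to meet the futility criterion, which the Discussion presents as the protection against needless exposure. The stated type 1 error and power would then describe a different set of patients from the one analysed.

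**Working it through.** **Inputs from the article.** p0 = 12%, p1 = 30%; futility cut-off 0.01 with prior Beta(0.30, 0.70); activity cut-off 0.90 with prior Beta(0.12, 0.88) (Study design). Interim at 10 patients in every cohort and also at 20 in D; final n of 20–25, equally likely, in A–C and 29 in D (Sample size).

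**Input not in the article.** f, the share of treated patients lost before one cycle. I assume 5% to 20%.

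**Step 1: the rules.** With r responders among n:

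- Activity if P(p ≥ 0.12 | Beta(0.12 + r, 0.88 + n − r)) ≥ 0.90. This needs 5 responders at n = 20–21, 6 at n = 22–27 and 7 at n = 28–29.
- Futility if P(p ≥ 0.30 | Beta(0.30 + r, 0.70 + n − r)) < 0.01. This means 0 responders at n = 10, and at most 1 at n = 20.

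**Step 2: reproduce the plan.** Exact binomial probabilities, with paths that stop for futility removed:

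- Stop at n = 10: 0.88^10 = 27.85% at a 12% rate and 0.70^10 = 2.82% at 30% (stated 27.8% and 2.8%).
- Cohort D, n = 29: type 1 error 5.02%, power 80.25% (stated 5.0% and 80.3%).
- Cohorts A–C, type 1 error for n = 20 to 25: (8.17 + 9.66 + 4.03 + 4.90 + 5.86 + 6.93)/6 = 6.59% (stated 6.6%). Mean power is 75.5% (stated 76%; the half-point difference does not affect this point).

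The stated figures therefore hold when every recruited patient is counted.

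**Step 3: remove early losses.** If the true rate among all treated patients is 12% and those lost are all non-responders, the rate among those analysed is 0.12/(1 − f). For f = 10% this is 0.12/0.90 = 13.3%. The design was re-run at that rate in two ways: (i) recruitment continues until the planned number is evaluable; (ii) recruitment is fixed and the evaluable number is Binomial(n, 1 − f).

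| f | Analysed rate | Type 1 error (i), A–C / D | Type 1 error (ii), A–C / D | Futility stop at n = 10 |
|---|---|---|---|---|
| 0 | 12.0% | 6.6% / 5.0% | 6.6% / 5.0% | 27.9% |
| 5% | 12.6% | 8.0% / 6.3% | 7.9% / 7.8% | 25.9% |
| 10% | 13.3% | 9.7% / 8.0% | 9.5% / 10.6% | 23.9% |
| 15% | 14.1% | 11.9% / 10.2% | 11.2% / 12.4% | 21.8% |
| 20% | 15.0% | 14.6% / 13.0% | 13.1% / 14.5% | 19.7% |

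The last column is [1 − 0.12/(1 − f)]^10, the chance of 0 responders among 10 analysed patients.

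**Step 4: single results.**

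- Cohorts A–C: 5 responders among 22 give a posterior of 0.897 (activity not declared). Dropping one early failure gives 5 among 21 and 0.913 (declared).
- Cohort D: 6 among 29 give 0.885 (not declared). Dropping two gives 6 among 27 and 0.913 (declared).

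**The case against.** Six points can be made for the plan.

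1. **The benchmark's denominator is unknown.** Study design describes the target only as "a response rate exceeding the historical response rate of p_0_ = 12% which was observed in a comparable pediatric patient population" treated in phase I/II trials. If that 12% was itself computed in patients with a minimum exposure, the comparison is like with like and the rate-driven inflation shrinks or disappears. This stands, so the type 1 error figures are conditional.

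2. **The early-loss fraction is unknown.** The article does not give f, and the full eligibility criteria are in an additional file. Progression is confirmed only after central review, some patients continue beyond progression, and toxicity is first handled by delay. All of this may keep f low. This stands for the size but not for the direction.

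3. **One cycle is not defined exactly.** A reader might take it as the priming week plus four full weeks, but the definition does not mention the priming week and sets no minimum number of doses. A looser reading shrinks the effect without removing it.

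4. **Different endpoints may use different sets.** This is true, and the wider set for PFS and OS is not in itself a contradiction. The phrase about enrolled patients also describes a boundary plot, whereas the analysis section defines the set. What remains is that the operating characteristics are computed at recruited numbers and the analysis is not.

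5. **Toxicity dropouts are not hidden.** A reader might infer that they are. The article does not support this: safety is part of the phase II primary objective, and PFS and OS include everyone who started treatment. Early failures are missing from one proportion, not from the trial's results.

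6. **The trial is exploratory.** Meeting the activity criterion stops nothing, futility goes to the DMC for advice, and the plan already accepts 6.6% in A–C. An exposure-based set is also common as a supportive analysis. This lowers the severity, but here the set is the primary one.

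**Conclusion.** The point holds in direction and is conditional in size. Any exclusion before one cycle removes essentially only non-responders, so it raises the observed rate and the chance of declaring activity.

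If 12% refers to all treated patients and evaluable numbers are kept at plan, type 1 error in A–C / D rises from 6.6% / 5.0% to 8.0% / 6.3% at f = 5% and to 14.6% / 13.0% at f = 20%. The chance of a futility stop at n = 10 falls from 27.9% to 23.9% at f = 10% and 19.7% at f = 20%, provided the one-cycle set is also used at interim. If interims instead count enrolled patients, as the Fig. 2 legend suggests, the interim is unaffected but interim and final use different denominators.

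A reader might conclude that the false-positive rate is certainly inflated by a known amount. The article does not support that, because it gives neither f nor the benchmark's denominator. This should be fixed, but it does not undermine the design.

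**What to change.** Define the primary activity population as all phase II patients who received at least one dose of study treatment at the RP2D. Count as a non-responder anyone without a centrally reviewed response within 6 cycles, with response as defined under Primary end point phase II (including its rule for calcified or intra-osseous sarcoma lesions). This covers early progression, death, toxicity and absent assessments. Use the same set at interim and final, so that the boundaries and the stated error rates apply to the patients analysed. Keep the one-cycle set as a sensitivity analysis, and state what exposure makes up one cycle and whether the priming week counts.

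The cost is a change of wording and a slightly less favourable observed response rate. No extra patients or data are needed, and treatment is unchanged.

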#### Secondary outcomes

(Confirmed immune-related) response will be evaluated separately for CR and PR, and SD and DCR will be evaluated in addition, also using iRECIST and iRANO. DOR will be evaluated for all patients who experienced (confirmed immune-related) response. Starting time point will be the time when best response was determined. The event-time endpoints PFS, OS and TTR will be estimated using the Kaplan-Meier method, considering all the patients who started the treatment, whatever their compliance to treatment, including if the treatment was stopped prematurely for a reason other than disease progression. 95%-confidence intervals will be provided for the Kaplan-Meier estimates.

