#### Primary end point phase II (outcomes)

Best response (CR or PR) will be based on Response assessment in neuro-oncology (RANO) criteria for all primary CNS tumors and Response evaluation criteria in solid tumors (RECIST) for non-CNS tumors, defined for each patient as the best response under study combination therapy during the first 6 cycles (assessment every 2 cycles) by central review. The proportion of responders will be reported as response rate.

Calcified or intra-osseous (osteo) sarcoma target lesions which were progressive before initiation of treatment and show SD on response evaluation (confirmation through a subsequent scan at least 4 weeks later) will be considered as a responder.

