#### Secondary end points (outcomes)

Duration of Response (DOR).Disease Control Rate (DCR).Stable disease (SD).Progression-free survival (PFS).Time to Response (TTR).Overall Survival (OS).Immune related Response Rate (RR) measured by immune-related RECIST (iRECIST) criteria and immunotherapy RANO (iRANO) criteria by central review.Entinostat plasma PK.

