### Dosing and dose adjustments

In this trial, nivolumab will be administered using the approved dose for adults, which is also the pediatric RP2D (3 mg/kg every 2 weeks) [40]. An ongoing phase I trial with entinostat monotherapy in children identified a RP2D of 4 mg/m2 weekly [41]. The recommended adult dose regimen is 5 mg weekly – 10 mg every 2 weeks (which equals 2.9 mg/m2 weekly – 5.8 mg/m2 every 2 weeks). The combination of entinostat, nivolumab ± ipilimumab was considered safe and tolerable in adults [42]. In the phase I part of the trial, entinostat has 2 dose levels: 2 mg/m2 and 4 mg/m2 (the latter reflecting the single agent pediatric RP2D). The dose escalation will be performed separately in both age groups.

After one so called priming week (to “prime” the immune system with entinostat before applying checkpoint inhibition) with 1 dose of entinostat on day 1, cycles of 4 weeks each will start with entinostat (orally) on day 1, 8, 15 and 22 and intravenous administration of nivolumab on day 1 and 15. Thereafter, every cycle follows the same schedule. There is no pause between cycles. All groups A – D will receive the same treatment.

The toxicity profiles of nivolumab and entinostat show a large overlap. Therefore, AEs will always be managed first by delaying nivolumab and entinostat administration together in combination with symptomatic treatment:
Phase I: After the occurrence of a DLT in phase I in dose level 2, it is allowed to de-escalate to dose level 1 (see Additional file 2) intra-individually if this is conform the dose-adjustment rules (provided in Additional file 3). If phase I patients do not tolerate dose level 1, treatment should be discontinued.Phase II: The dose de-escalation scheme is depicted in Additional file 2. For patients in dose level 1 it can be considered to de-escalate to nivolumab monotherapy (dose level − 1). If this is also not tolerated, treatment should be discontinued. Treatment modifications for toxicity are described in Additional file 3.

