### Assessments and collection of outcomes

An overview about diagnostic and therapeutic measures, timing of disease assessment, and study visits is displayed in Additional file 4. In brief, routine visits are planned weekly during the first 2 cycles and every 2 weeks thereafter. Response assessments are scheduled every 8 weeks.

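### Read literally, the duration-of-response clock starts at the best rather than the first response, so a PR that deepens to CR loses 8 or 16 weeks of DOR

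*Protocol article*

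**What the plan says.** The rule for DOR is in the protocol article, Statistical methods, Secondary outcomes. The population comes first: "DOR will be evaluated for all patients who experienced (confirmed immune-related) response". The origin of the clock follows: "Starting time point will be the time when best response was determined". The same section keeps the two levels of response apart: "Confirmed immune-related) response will be evaluated separately for CR and PR".

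Best response is defined under Primary end point phase II as "the best response under study combination therapy during the first 6 cycles (assessment every 2 cycles) by central review". That section also counts as responders certain patients with calcified or intra-osseous sarcoma lesions that were progressing before treatment and then show confirmed stable disease.

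The timing comes from two other sections. Dosing and dose adjustments sets a one-week priming period and then "cycles of 4 weeks each will start with entinostat (orally) on day 1, 8, 15 and 22". Assessments and collection of outcomes adds: "Response assessments are scheduled every 8 weeks".

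DOR is listed among the secondary end points. The article defines its start nowhere else.

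**The concern.** Best response, as defined, is a maximum over up to three scheduled assessments, and its categories are ordered. The date on which the maximum is reached can therefore fall after the date on which the patient first responded. A clock that starts at the maximum drops the time already spent in response, and drops it only for patients who improve further.

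The error has one direction. The rule can leave a DOR unchanged or shorten it, but cannot lengthen it. It also reverses the natural ordering, because a PR that becomes a CR is credited with less durability than an identical PR that does not. The article plans to compare patient outcomes between group D and groups A to C, and with matching registry groups. If DOR is among those outcomes, a group with more deepening responses would look less durable for that reason alone.

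**Working it through.** The article gives no DOR figure to reproduce, so the check is date arithmetic on its schedule.

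**Inputs**
- Priming period: 1 week; cycle length: 4 weeks (Dosing and dose adjustments).
- Assessment every 2 cycles, best response taken over 6 cycles (Primary end point phase II), so 6 / 2 = 3 scheduled assessments.
- Assessment interval: 8 weeks (Assessments and collection of outcomes), which agrees with 2 × 4 = 8.

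**Assessment times**, counting the priming week: 1 + 8 = 9, 1 + 16 = 17 and 1 + 24 = 25 weeks. Whether the priming week is counted does not matter below, since only differences are used.

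**Formula.** With the same end date under both rules:

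loss = (end − first response) − (end − best response) = best response − first response.

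| First response (week) | Best response (week) | DOR lost (weeks) |
|---|---|---|
| 9 | 9 | 0 |
| 9 | 17 | 8 |
| 9 | 25 | 16 |
| 17 | 17 | 0 |
| 17 | 25 | 8 |
| 25 | 25 | 0 |

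**Two patients compared.** Assume that both have PR at week 9 and progress at week 49.
- One stays in PR: DOR = 49 − 9 = 40 weeks under either rule.
- The other reaches CR at week 25: DOR = 49 − 25 = 24 weeks under the literal rule, against 49 − 9 = 40 weeks from first response.

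Onset and progression are the same, and the deeper responder is credited with 16 weeks less.

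**Does the cohort median move?** It depends on which patient deepens. Take five uncensored DORs, measured from first response, of 8, 16, 24, 32 and 40 weeks (assumed values; median 24).
- If the 40-week patient loses 16 weeks, the values are 8, 16, 24, 24 and 32, and the median stays at 24.
- If the 24-week patient loses 8 weeks, the values are 8, 16, 16, 32 and 40, and the median falls to 16.

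**How many responders?** With 20 to 25 patients in groups A to C and 29 in group D (Sample size), the 30% target rate gives 20 × 0.30 = 6 to 25 × 0.30 = 7.5, and 29 × 0.30 = 8.7. The 12% historical rate gives 20 × 0.12 = 2.4 to 25 × 0.12 = 3.0, and 29 × 0.12 = 3.5. The article does not state the share of these that would go from PR to CR.

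**The case against.** The strongest reply is that best response is also used as the name of a yes/no status. The primary endpoint is introduced as best response with CR or PR in brackets, the proportion of responders is the response rate, and the design and analysis sections speak of best response rates. On that usage, the time when best response was determined could simply mean the time when the patient was found to be a responder, and no time would be lost. This reading is possible. It is not what the sentence literally says, given a best response taken over six cycles and CR and PR evaluated separately. If it was the intention, the sentence still permits two start dates and needs rewording.

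The limits on the effect also stand. DOR is secondary and descriptive. No test, futility or activity boundary, or sample size uses it. Response is assessed at each follow-up scan, so first-response dates can be recovered at analysis.

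A reader might infer more than the article supports. One inference is that one or two deepening patients will move a cohort median; the example above shows that this can happen but need not, and the number of such patients could be zero. Another is that the resulting DOR cannot be set beside time to response or the DOR of other trials. The article does not define the event for time to response and says nothing of how other trials measure DOR, so neither claim can be made from it.

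**Conclusion.** The point holds as a badly fixed definition of a secondary endpoint. Taken literally, the rule discards 8 weeks of time in response when the best category is reached one assessment after the first response, and 16 weeks when it is reached two assessments after. Nobody else's DOR changes, and no DOR is lengthened.

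These sizes assume that scans are on schedule, that the end date is the same under either rule, and that the six-cycle window of the primary endpoint also governs best response for DOR. The article does not restate that window for the immune-related version, so 16 weeks is the maximum only if it carries over. The effect on any cohort summary cannot be stated, because the frequency of PR deepening to CR is not given.

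It would be wrong to infer that the trial's activity conclusions are at risk. The primary response rate counts responders irrespective of when they responded within the window, and the start of the DOR clock plays no part in it.

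**What to change.** Replace the start-time sentence with a rule tied to first response:
- DOR starts on the date the patient first met the responder definition by central review, that is, the first documented CR or PR under RECIST or RANO.
- For the immune-related version, it starts at the first iCR or iPR that was later confirmed.
- For the sarcoma patients counted as responders on stable disease, it starts at the first stable-disease assessment that was later confirmed. A rule that named only CR and PR would leave them without a start date.

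Report depth of response (PR, CR, and PR deepening to CR) separately. The cost is a short rewording before DOR is analysed. All imaging already goes to central review and response is assessed at each follow-up scan, so no new data are needed.
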